# Study protocol for a stepped-wedge implementation study investigating the intersectoral collaboration of implementing the TREAT INTERACT intervention for primary school teachers and the mhGAP for health care workers for child mental health promotion in Uganda

**DOI:** 10.1186/s13063-024-08312-5

**Published:** 2024-07-09

**Keywords:** Adolescents, Children, Global mental health, Implementation, Low- and middle-income countries, Primary schools, Task-sharing, Teachers, Uganda

## Abstract

**Background:**

Mental and neuropsychological disorders make up approximately 14% of the total health burden globally, with 80% of the affected living in low- and middle-income countries (LMICs) of whom 90% cannot access mental health services. The main objective of the TREAT INTERACT study is to adapt, implement, and evaluate the impact of a novel, intersectoral approach to prevent, identify, refer, and treat mental health problems in children through a user centred task-sharing implementation of the TREAT INTERACT intervention, inspired by the World Health Organization (WHO) Mental Health Gap Action Programme Intervention Guide (mhGAP-IG) for primary school staff in Mbale, Uganda. Health care personell will be trained in the mhGAP-IG.

**Methods:**

This is a pragmatic mixed-methods hybrid Type II implementation-effectiveness study utilizing a co-design approach. The main study utilize a stepped-wedged trial design with six starting sequences, randomizing three schools to the intervention at each interval, while the remaining act as “controls”. Other designs include a nested prospective cohort study, case control studies, cross-sectional studies, and qualitative research. Main participants’ outcomes include teachers’ mental health literacy, stigma, and violence towards the school children. Implementation outcomes include detection, reach, sustainability, and service delivery. Child and caregiver outcomes include mental health, mental health literacy, and help-seeking behaviour.

**Discussion:**

Based on the results, we will develop sustainable and scalable implementation advice on mental health promotion and draft implementation guidelines in line with current WHO guidelines. This project will generate new knowledge on the structure, organization, delivery, and costs of mental health services in a LMIC setting, as well as new knowledge on the implementation and delivery of new health services.

**Trial registration:**

ClinicalTrials, NCT06275672, 28.12.2023, retrospectively registered.

**Supplementary Information:**

The online version contains supplementary material available at 10.1186/s13063-024-08312-5.

## Background

Mental health challenges present a high global burden, with stigma, inequity, poverty, and low prioritization of mental health care at a health systems level contributing to a relatively higher burden in low- and middle-income settings [1]. More than 80% of people with a mental health disorder live in low- and middle-income countries (LMICs). In Uganda, only 1% of the total health expenditure is used for mental health, including child and adolescent mental health (CAMH) [2]. Furthermore, there is a general lack of services and access to evidence-informed services, and it takes, on average, 17 years for only 14% of all research to reach the practice field [3]. Implementation research, “the scientific study of methods to promote the systematic uptake of research findings and other evidence-based practices (EBPs) into routine practice”, can help close this gap with particular relevance for LMICs [4, 5] when working towards universal health coverage [6]. Building on implementation science, mental health system strengthening and intersectoral collaboration between the health and other sectors [7], such as education, has the potential to increase both coverage and effectiveness of mental health care [8, 9]. In line with recommendations in the implementation science field, engaging key stakeholders and service users in mental health interventions is critical to empowering the workforce, enhancing mental health literacy, and combating stigma [8, 10, 11].

Education is a powerful tool to increase mental health literacy and break the stigma associated with mental health. Also, the school provides an opportunity for reaching children in need of services and following children over time [12]. Good child and adolescent mental health in countries with low-resourced health systems depends on the integration of health and education [13]. Healthy school environments are assumed to be related to improved education outcomes, and as such, there is an interdependence between good education and good child and adolescent development [14]. A systematic review of mental health promotion interventions in LMICs identified 22 studies during a 13-year period (2000–2013), including 14 school-based studies indicated that interventions aimed at promoting child and adolescent mental well-being can be implemented in school and community settings in LMICs with a positive impact on mental health outcomes [15]. A more recent systematic review, published in 2021, of universal school-based programmes focusing on anxiety and/or depression among children aged 6–18 years in LMICs identified six studies, most of which had clear methodological weaknesses [16] pointing towards a knowledge gap. Family and parenting interventions have also been employed to improve child and adolescent mental health (CAMH) in LMICs; however, a systematic review from 2019 revealed merely 36 papers on the topic [17]. Although research on services is scarce, we acknowledge that reviews may not fully capture the “reality on the ground” because the so-called “grey” literature or unpublished material is excluded. Yet, there is a clear scarcity of high-quality studies on CAMH and school-based interventions to promote child and adolescent mental health in LMIC primary schools.

Uganda has the highest proportion of children in the world, with nearly half of the population (47% or approximately 20 million) below the age of 15 [18]. A systematic review and meta-analysis including 26 papers found a prevalence of any mental disorder in Uganda of 22.9% in children, with anxiety disorders (14.4%) and depressive disorders (22.2%) being the most common [19]. Furthermore, many children are exposed to violence and trauma, which are important determinants of mental health problems [20]. In a study with 5804 children and adolescents aged 13–17 years in Uganda, 25% of girls and 11% of boys reported sexual abuse, 59% of boys and 44% of girls reported physical violence, and 20% of both girls and boys reported emotional violence [21]. Many children in Uganda also experience violence at school. In a representative sample of 3706 primary school children, 55% reported violence by their teacher [22]. However, fewer than 10% of children and adolescents who experience sexual abuse or physical violence receive help from health care services despite scoring significantly higher on mental distress than the non-exposed [21]. Child and adolescent mental health has been recognized as a serious public health and development issue by the Ugandan Government since the development of CAMH policy guidelines in 2017 [23]. Yet, in a scoping review including studies on CAMH services in Uganda [24], we described a limited set of mental health interventions launched between 2009 and 2019.

As in most sub-Saharan countries, the critical barriers to mental health provision in Uganda are a lack of resources and systems for referrals, stigmatizing attitudes, and a lack of help-seeking [25]. As of 2022, there were about 50 practicing psychiatrists in Uganda [26]. In 2017, only seven were trained in child and adolescent psychiatry, serving the country’s 20 million children [24]. Specialized clinical officers and nurses with shorter training primarily provide existing services. Task-sharing or task-shifting is practiced mainly by specialized and less specialized workers (e.g., with shorter training and fewer health care qualifications) [27, 28]. This results in work overload, inadequate training and supervision, and non-compliance with relevant guidelines [29].

As one of the strategies to build capacity and improve access to care, the Ugandan CAMH policy guidelines suggest “to establish mental, neurological and substance use services in schools and other institutions where children and adolescents are cared for.” While a school health workforce exists in Uganda, it fulfills in particular preventive measures in terms of vaccination, hygiene, and sporadic curative tasks. It runs ad hoc health information campaigns and similar tasks related to hygiene and somatic and reproductive health, while mental health remains largely neglected in such initiatives. Similar to the Ugandan health system, the education sector is under-resourced and faces implementation challenges at scale. The mainstream health care system provides access to children up to 5 years, subsequently there is a loss of contact during primary school age. The primary school setting has the potential to be an important arena for task-sharing interventions, with an enrolment rate of 98%, even if only 61% of children completed primary school in 2017 and only 32% completed without drop-out or repetition. Programmes that seek to change the behaviour of students and/or the current organization of schools (including timetabling, infrastructure, policies, and practices) require more intensive integration and collaboration than those which include only an educational or awareness-raising component [30]. Research is needed to understand how task-shifted mental health interventions can be implemented and sustained over time [31], their *acceptability and feasibility* among the workforce [28], their readiness to task shift, and how task-sharing can effectively address the mental health treatment gap.

The Mental Health Gap Action Programme Intervention Guide (mhGAP-IG) was first launched by the World Health Organization (WHO) in 2010 [32] and updated as mhGAP-IG Version 2.0 in 2016 [33]. This version revised the Child and Adolescent Mental Health Disorders model, which now covers developmental, behavioral, and emotional disorders among the target population, including middle childhood (6–12 year olds). It has a context-oriented approach, including general health care, carer, school, and the larger community. The mhGAP intervention aims to bridge the mental health treatment gap in countries with limited resources to achieve universal health coverage. Between 2012 and 2016, World Vision Uganda, together with the WHO and Uganda Ministry of Health, implemented a pilot mhGAP-IG project in three districts (Jinja, Kamuli, and Kitgum) in Eastern and Northern Uganda [34]. In 2016, a district mental health care plan was developed, and its integration into primary care was evaluated as “feasible” in the Kamuli district in Uganda [35]. These initiatives were predominantly focused on adult mental health, and mhGAP-IG has not been scaled up to other districts. Our study group has previously tested the applicability of the CAMH component of the mhGAP-IG in Uganda [36]. We found that the knowledge gain was equally high for nurses and clinical officers following 5 days of training, with initial but not prolonged changes in their practice. We believe this was due to a lack of focus at the system level on how this programme should be implemented sustainably, and concluded that supervision and “further task-sharing studies integrating CAMH into a larger sample of primary health care clinics are suggested, including a community mobilization component in the intervention to improve CAMH clinic attendance” [36].

In general, referral of children with mental health conditions to the public health system is very low in Uganda. This is partly due to a lack of available services and to stigma related to mental health problems [25] both at the health care system level and among community members [37, 38]. There is limited integration of mental health services into the existing health services and schools, and merely sporadic communication between services and sectors. Due to schools’ lack of operative resources, collaboration with other sectors has received little attention. However, a few intersectoral programmes have been scaled up and evaluated as effective [14, 28]. In Uganda, and to our knowledge in sub-Saharan Africa, CAMH is yet to be included in the tasks shared with the shifted education sector.

### Objectives

The overall aim of the TREAT INTERACT study is to adapt, implement, and evaluate the impact of the education and health interactive TREAT INTERACT intervention to prevent, identify, refer, and treat mental health challenges in children and adolescents in Uganda through a user-involved co-design approach. Our specific objectives are related to improving children’s mental health while simultaneously strengthening the education system’s handling and response of children with challenges as well as the intersectoral collaboration between health and education.

## Methods

### Trial design

TREAT INTERACT will use a co-design approach where the research group and key stakeholders will collaborate at all stages of the research process according to implementation science theory and participatory action research. The study is designed as a pragmatic mixed-methods, Hybrid Type II Implementation-Effectiveness study [39], including dual testing of intervention effectiveness and evaluation of the implementation strategy using multiple study components. The SPIRIT reporting guidelines are adhered to [40] (see also Fig. 1).

**Fig. 1 Fig1:**
[figure not shown]
SPIRIT schedule of enrolment, interventions, and assessments. **See Supplementary material Tables 1 and 2

Implementation science often relies on frameworks because of practical flexibility to facilitate implementation efforts [41]. The research will be directed by the consolidated framework for implementation research (CFIR) [42]. CFIR suggests consistent terms and definitions to make them applicable and enhance the generalizability of findings across settings, within and outside health care. In addition, the project will be organized within the Exploration, Preparation, Implementation, and Sustainment (EPIS) framework [43]. EPIS will be used as a conceptual tool to organize the various phases in the implementation process and different interrelated inner and outer factors likely to influence the implementation. Proctor’s [44] Implementation (acceptability, adoption, appropriateness, costs, feasibility, fidelity, penetration (reach), and sustainability), Service (efficiency, safety, effectiveness, equity, patient-centeredness, timeliness), and Client (satisfaction, function, symptomatology) Outcomes will guide the evaluation. We will strive towards making the intervention *gender-*sensitive, thus challenging potential socially constructed gender roles that might impact mental health in general, and when targeting gender-based violence in particular [45]. The intervention will also be *trauma*-sensitive by incorporating trauma and responses to trauma-exposure.

### Patient and public involvement

The research proposal was developed based on the TREAT consortium’s previous research within the same context. Key stakeholders were involved immediately after receiving funding to inform the development of the TREAT INTERACT intervention, and implementation strategies. The key stakeholder group were not involved in choice of outcomes measures or recruitment; however, they will be actively involved throughout all steps of the project.

### Study setting

The study will take place in Mbale District in Eastern Uganda, which was recently split into two administrative units: the District and the City. Mbale is located approximately 250 km northeast of Kampala. It has a population of approximately 500,000 people, half younger than 15 years. Eighty-six percent of those aged between 6 and 12 years attend primary school. Nearly all (97%) of the population live within 5 km of a primary school, and 94% live within 5 km of a public health facility.

Health care services are provided at five different levels: Level 1. Village health teams, Levels 2–4. Health centres II, III, IV, Level 5. Hospitals, and a regional referral hospital with a mental health unit. In Uganda, the administration of Districts is further divided into sub-districts, consisting of parishes. Villages are the smallest administrative unit. We will include a sufficient number of “sub-districts” that include primary health clinics (levels II, III), their respective hospital for supervision and referral (Mbal(e Regional Referral Hospital), and the relevant adjacent schools.

Within the health system, this study will target health workers at level III health centres who will be trained in the prevention and early identification of mental health problems, while those from health centre IV and hospital levels will receive extra training through the TREAT INTERACT in psychological and pharmacological treatment of childhood mental disorders and how to provide support and supervision to the teachers. At the district level, we will work with stakeholders in education, health, administration, and the police as well as the policy-makers to ensure sustainability in the referral system.

### Data collection and management

Data collection will be done on electronic devices by trained data collectors using the Open Data Kit (ODK) system and uploaded and stored on a Makerere University-based server. All data entered into the trial database via ODK will be subject to validation (number, date ranges, etc.) to assure the quality of the resulting dataset. Important trial documents and databases will be archived for at least three years after completion of the clinical trial. Data collectors will thoroughly review the consent form with teachers at the school prior to data collection. Data collectors review the consent and assent form individually with caregivers and children as well and specify what type of questions will be asked. Throughout data collection, it is made very clear that participants can choose to withdraw at any time or not answer every question.

Qualitative data will be stored and backed up in predefined data management systems within Makerere. A data-sharing contract is elaborated between the institutions. The statisticians, PIs, and PhD students will serve as a data monitoring committee and have access to the interim results to monitor the data collection and the final dataset. Midway in the data collection, the same team will be auditing the trial process, including enrolment, consent, intervention adherence, and data completeness. This trial does not involve collecting biological specimens for storage.

### Work packages

This project is divided into four work packages (WPs). WP2 is the largest in terms of allocated resources and data collection efforts and comprises a stepped-wedge randomized controlled design. The work packages are:WP1: Intervention and implementation mappingWP2: School implementationWP3: Intersectoral collaborationWP4: Sustainability

#### WP1: intervention and implementation mapping

The main objective of this work package was to develop a school intervention, the TREAT INTERACT intervention, inspired by the mhGAP-IG and develop implementation strategies among the stakeholders in primary schools in Mbale to inform the policy formulation and implementation of mhGAP in the health centres and the TREAT INTERACT in the schools to ensure that the education and health system has similar understanding of child mental health promotion and treatment. An implementation map is made to document the process from the initial exploratory phase until evaluation and dissemination. Data will be collected using mixed methods, and a theory of change will be created through a participatory approach with user involvement. Interviews will be conducted in English and transcribed verbatim. For our project, we have started by mapping stakeholders in the field of child and adolescent mental health (child and adolescent specialists from different sectors, police, and policy professionals). Consultative meetings are held with these stakeholders to guide the development of the TREAT INTERACT intervention and to assess its suitability for the planned trainings.

Together with these stakeholders, a root cause analysis is done to establish the root causes of the current situation of mental health service delivery for children and adolescents. Through this participatory approach with stakeholders in child and adolescent mental health, we aim to set the ground for participation, ownership, and collaboration between the various sectors for the improvement of referral systems and mental health outcomes among school-going children [46].

#### WP2: school implementation

In this work package, the project will estimate the effect of the TREAT INTERACTION school intervention among teachers on implementation and client outcomes in primary schools in Mbale to inform the implementation of child and adolescent mental health services. Specifically, we shall measure the readiness and level of reach of child and adolescent mental health services in Mbale. We shall also determine which implementation strategies are associated with the sustainability of the TREAT INTERACT school training programme in primary schools and the health sector in Mbale.

The quantitative aspects in this work package will be a stepped-wedge cluster randomized trial to randomize 18 schools into six cohorts of three schools. Using the stepped-wedge design will allow every participant to receive the intervention. All cohorts will contribute data throughout 21 months, during both the control and intervention phases. All cohorts will provide data at baseline before any of the schools receive the intervention, at month 0, and then repeatedly every three months adjusted for school terms. Cohort 1 will receive the intervention at month 0; cohort 2 at month 3, cohort 3 at month 6, cohort 4 at month 9, cohort 5 at month 12, and cohort 6 at month 15.

The primary outcomes in this work package will be the effect of task-sharing using the TREAT INTERACT school programme on stigma, mental health literacy, and violence. The 18 schools are systematically selected using STATA and according to two strata: urban or rural location and public or privately owned schools. All teachers will be enrolled for study participation. This will be an open-cohort study where new employees, starting employment after the intervention has been rolled out, will be instructed to complete an information meeting within 4 weeks following their employment, and then take part in the remainder of the data collection. New training courses will be provided to new entrants when needed.

##### Eligibility criteria

Participants eligible for the trial must comply with any of the following at randomization: A teacher/ staff member at a preselected primary school in Mbale. Child-caregiver pairs are eligible when a learner is enrolled in a selected primary school in Mbale, the child has a caregiver living with her or him and provides ascent, and the caregiver with a child in the selected school provides informed consent.

##### Sample size

Power analyses were conducted in R [47] using the calcPower.SWD function in the samplingDataCRT package and indicated acceptable power, at least 80%, for realistic effect sizes in a stepped wedge design with cluster (school) as a random effect. Longitudinal inclusion of teachers is assumed since it is assumed that most teachers will stay in the schools during follow-up. This model assumes that the within-cluster variance, between-cluster variance and the error variance are equal. Based on the expected sample size of 10 teachers per school, we can expect to detect a treatment effect of 0.2, which is considered a small effect size. However, since preliminary analysis of the situation showed fewer teachers at most schools, a decrease that became apparent during Covid-19, all teachers in the sampled schools will be included in the study.

For the child-caregiver pairs, a sample size of 388 was found sufficient to detect a proportion difference of 0.50 compared to 0.30 with 80% power and 10% loss to follow-up [48]. A stratified sampling proportional to the student population size in each school is used to determine the number of child-caretaker pairs to be included per school. To measure the impact of the intervention among teachers on the community, child-caretaker pairs will be enrolled in a mixed methods design with a nested prospective cohort study to collect quantitative data and conduct focus group discussions and key informant interviews. For the nested prospective cohort, individual study units (child-caretaker pairs) will be selected using systematic sampling. We shall obtain the registration lists of each cohort from the selected primary schools in Mbale. The sampling will start by selecting an element from the list at random (random starting point = P) using computer-generated random numbers. Every K^th^ element in the frame will be selected, where K is the sampling interval. The individuals selected for study enrolment will be done as follows:

First respondent will have the number = P, 2nd respondent will have the number = P + K, 3rd respondent will have the number = P + K + K. The selection process will be continued until the number of study units (388 child-parent pairs) required per school is attained. At the same time, sex and age-stratified focus group discussions and stakeholder key informant interviews will be employed to collect qualitative data. The mixing of methods aims to establish corroboration of data and will be a concurrent triangulation design.

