##### Retention

To mitigate both non-retention and non-adherence, once the teachers are enrolled or randomized, the study site will make an effort to follow them for the entire study period. It is projected that the rate of loss-to-follow-up on an annual basis will be at most 5%. Study site staff will develop and implement local standard operating procedures to achieve this level of follow-up.

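### The only power statement for the teacher outcomes assumes 10 teachers per school, which the next sentence says most schools do not have, and it is not recomputed

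*Protocol article*

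**What the plan says.** Under WP2: school implementation, the design is "a stepped-wedge cluster randomized trial to randomize 18 schools into six cohorts of three schools", and stigma, mental health literacy and violence are named as the primary outcomes of that work package.

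Under Sample size, power was computed in R and "indicated acceptable power, at least 80%, for realistic effect sizes in a stepped wedge design with cluster (school) as a random effect". The variance inputs are described only in relation to each other: "This model assumes that the within-cluster variance, between-cluster variance and the error variance are equal". The teachers are treated as a followed cohort: "Longitudinal inclusion of teachers is assumed since it is assumed that most teachers will stay in the schools during follow-up". The result is then stated: "Based on the expected sample size of 10 teachers per school, we can expect to detect a treatment effect of 0.2", with 0.2 described as small.

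The sentence after that qualifies the input, "since preliminary analysis of the situation showed fewer teachers at most schools", and says that every teacher in the sampled schools will therefore be taken in. No new teacher count, power or detectable effect is given there or elsewhere. The other sample size in the section, 388, concerns child-caregiver pairs. The Randomization section fixes the number of schools at 18.

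**The concern.** The power claim and the correction to its main input stand side by side, and the claim is left unchanged. Enrolling everyone is a census. It gives each school its true size, and a school with 6 teachers then contributes 6. With the schools fixed at 18, the number of clusters cannot make up the difference.

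This is the only quantitative justification for the primary teacher outcomes. If the real teacher numbers are well below 10, the effect the trial can reliably detect is larger than 0.2. A null result could then be read as evidence against a small effect that the trial was not placed to detect.

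The scale of 0.2 adds to the difficulty. The three variances are said to be equal but no value is given, so a reader cannot tell whether 0.2 is a fraction of the total SD or is measured in units where each component equals 1. The two readings give very different power.

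**Working it through.** **Inputs from the protocol article.** 18 schools in 6 sequences of 3; 10 teachers per school (18 × 10 = 180); effect 0.2; power at least 80%; three equal variances; the same teachers followed over time. Rounds: months 0 to 21 every three months, 21/3 + 1 = 8, which agrees with the baseline, six collections and follow-up listed under WP3 Design.

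**Assumptions, because the text does not state them.** Two-sided 5% test with a normal reference; fixed round effects; the three variances read as school (s1), teacher within school (s2) and residual (s3); the first sequence has one control round.

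**Method.** For a school with m teachers, the vector of its round means has covariance V = s1·J + (s2/m)·J + (s3/m)·I, where J is the all-ones matrix and I the identity. The SE of the treatment effect is the square root of the treatment element of the inverse of ΣX′V⁻¹X over the 18 schools. Then:

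- power = Φ(0.2/SE − 1.960)
- effect detectable with 80% power = (1.960 + 0.842) × SE = 2.802 × SE

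**The plan's own figure, with 0.2 in total-SD units (s1 = s2 = s3 = 1/3).** At m = 10, SE = 0.0550, so 0.2/0.0550 − 1.960 = 1.68 and power is 95%. This meets the stated lower bound of 80%. An exact reproduction is not possible, because the plan gives only a bound and does not state the test level or the variance values.

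**The same model with fewer teachers in every school:**

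| Teachers per school | SE | Power for 0.2 | Detectable effect (80% power) |
|---|---|---|---|
| 10 | 0.0550 | 95% | 0.154 |
| 8 | 0.0615 | 90% | 0.172 |
| 6 | 0.0709 | 80.5% | 0.199 |
| 5 | 0.0776 | 73% | 0.217 |
| 4 | 0.0867 | 64% | 0.243 |

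With 7 rounds instead of 8, power is 94% at 10, 77% at 6 and 70% at 5.

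**The other reading of the scale (s1 = s2 = s3 = 1).** Every SE is multiplied by √3 = 1.732. At m = 10, SE = 0.0953, so 0.2/0.0953 − 1.960 = 0.14 and power is 56%, with a detectable effect of 0.267. At m = 6 power is 37%. On this reading 0.2 is 0.2/1.732 = 0.115 of a total SD.

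**Unequal schools.** The text says most schools are smaller, not all. Three illustrative mixes, with sizes allocated at random to sequences and components of 1/3, give these mean powers:

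- 11 schools with 5 teachers and 7 with 10 (125 teachers): 86%
- 12 schools with 5 and 6 with 12 (132 teachers): 87%
- 11 schools with 7 and 7 with 14 (175 teachers): 95%

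These mixes are assumptions, as are the uniform sizes in the table.

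**The case against.** The strongest defence is that nothing has been shown to be miscalculated. On the standardised reading, 10 per school gives 95%, so there is slack down to about 6 teachers in every school before 80% is lost. Describing 0.2 as small fits that reading. The text says most schools, not all, and a census lets larger schools supply more than 10, so the claim may survive. The article also discloses the shortfall openly. All of this stands, and it limits how far the point goes. It does not remove the point: the claim is still tied to 10 per school, and the reader is given no count with which to judge whether the slack suffices.

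A reader might go further and infer that the trial is underpowered. The documents do not support that, since no actual count is given and plausible mixes stay above 80%.

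A reader might also count attrition of up to 5% a year as a further loss. But WP2 describes an open cohort in which new staff join data collection, so leavers are at least partly replaced.

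One could also add school-by-round variation or a small-sample reference distribution, either of which lowers power. The values needed are not in the protocol, and the detail of the analysis model belongs to an analysis plan that is not shown. Neither is part of this point.

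**Conclusion.** The point holds as an unrepaired inconsistency in the sample-size justification for the primary teacher outcomes. The stated basis of 10 per school is contradicted for most schools in the following sentence, enrolling all teachers does not restore it in those schools, and no new figure is given.

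Whether 80% power for 0.2 is retained cannot be settled from the documents. Under the assumptions listed, on the total-SD reading, it is retained if schools have about 6 or more teachers throughout, or if larger schools offset smaller ones; it is lost at a uniform 5 or fewer. If each component equals 1, it was not reached even at 10. The point should be corrected, but it is not grave enough to call the design into question.

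**What to change.** Rerun the existing R calculation with the actual number of teachers in each of the 18 schools. The Randomization section says the school list records teacher numbers, and Trial status says recruitment began in September 2023, so the counts should be available. Replace the 10-per-school statement with the resulting power for 0.2 or the resulting detectable effect, and say in what units 0.2 is expressed. If the actual counts do not give 80% power for 0.2, withdraw that claim and report the effect that can be detected.

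No extra schools or teachers and no change to the analysis model are required. The cost is one rerun, a few reworded sentences and possibly a less favourable published figure.
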